### 2.4. Sample Size Calculation

#### 2.4.1. tDCS-Based Study

The simple size for the tDCS-based study was calculated using G*Power software (version 2.1, Heinrich-Heine-Universität Düsseldorf, Düsseldorf, Germany), taking into consideration the design of two intervention groups and three assessment times. The primary outcome was chosen to be King’s Parkinson’s Disease Pain Scale with an estimated effect size of F = 0.25. An α level of 0.05 and a power of 90% was assumed, with a total sample of 28 subjects estimated. Considering a 15% follow-up loss, we estimated a minimal sample size of 32 patients, with a minimal recruitment of 16 required for each of the intervention groups.

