#### 2.4.2. AO+MI-Based Study

The simple size for the AO+MI-based study was calculating taking into consideration the same parameters as tDCS-based study. It being estimated the same sample size of 32 patients.

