### 2.5. Data Analyses

The SPSS software package (version 25.00; SPSS inc., Chicago, IL, USA) will be used by a blinded statistician for statistical analysis of the data. Demographic and clinical variables will be presented as mean and standard deviation. A 95% confidence interval (CI) will be taken, considering statistically significant all those values that had a *p* < 0.05. Parametric statistical tests will be used for hypothesis testing (*n* > 30). To show differences in the main variables, an analysis of variance (ANOVA) 2 × 3 of repeated measurements will be carried out taking time and group as factors, being the groups active-tDCS (a-tDCS) vs. sham-tDCS (s-tDCS) in the tDCS-based study and AO+MI-BCI vs. AO-control AO+MI-based study, and the measurements times pre-treatment, post-treatment, and at 15 days post-treatment. If significant differences are found in any of the interactions, a post hoc analysis will be performed with Bonferroni correction. The effect sizes will be calculated by means of the d of Cohen, being classified as small (d between 0.20 and 0.49), medium (d between 0.50 and 0.79), or large (d greater than 0.80) following the method of Cohen.

For the rest of the psychological variables, a Pearson’s correlation with the physical variables will be carried out in order to find relationships between both. Low correlation will be taken as that with values between 0.2 and 0.39; the correlation will be considered moderate when the value goes from 0.40 to 0.79; and high when the value of the correlation is greater than 0.80.

For the analysis of neurophysiological variables rMT, MEP magnitudes will be determined by averaging peak-to peak amplitudes. The ratio of the rMT, MEP amplitude recorded at each post-intervention time-point relative to the baseline rMT will be calculated [(MEP amplitude at each stage–baseline MEP amplitude)/baseline MEP amplitude Å~100]. Statistical analyses will be performed on the calculated test-to baseline MEP ratios. For the CSP values the time will be measured manually in each trial and averaged and the ratio compared to baseline measurement will be also calculated.

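### The 90% power stated for 28 subjects holds only if the unstated between-visit correlation is about 0.61 or higher, and 32 recruited leave 27, not 28, after 15% loss

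*Protocol article*

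**What the plan says.** Section 2.4.1 of the protocol article bases the calculation on the King's Parkinson's Disease Pain Scale, "taking into consideration the design of two intervention groups and three assessment times". The planning effect size is F = 0.25. The result follows: "An α level of 0.05 and a power of 90% was assumed, with a total sample of 28 subjects estimated". Loss is then added: "Considering a 15% follow-up loss, we estimated a minimal sample size of 32 patients". This is split into at least 16 per arm.

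Section 2.4.2 uses the same parameters for the AO+MI trial: "It being estimated the same sample size of 32 patients".

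Section 2.5 names the analysis that this power should describe: "an analysis of variance (ANOVA) 2 × 3 of repeated measurements will be carried out taking time and group as factors", with post hoc comparisons if an interaction is significant. The test that answers the treatment question is therefore the group-by-time interaction.

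Neither section gives the correlation between repeated measurements or a nonsphericity correction, and the sample size section does not say which effect of the ANOVA was powered.

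**The concern.** In a repeated-measures design the power for group by time depends on the correlation between visits as strongly as on the effect size. The article presents 28 subjects as the result of a calculation, but the inputs it lists do not fix a result. With the commonly used correlation of 0.5 they give about 81% power, not 90%.

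The loss step adds a smaller problem. The paragraph requires 28 evaluable subjects, but its recruitment figure does not leave 28 at the loss rate it assumes.

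Both trials rest on this one paragraph. If the correlation is nearer 0.5 than 0.6, the chance of missing an effect of the planned size is about 1 in 5 instead of 1 in 10, and a negative result from either trial would carry less weight than the stated power suggests.

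**Working it through.** **Inputs from the article:** k = 2 groups, m = 3 assessments, f = 0.25, alpha = 0.05, N = 28 evaluable, 15% loss, 32 recruited (16 per arm).

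**Assumed, because not stated:** the effect tested is the group-by-time interaction; epsilon = 1 (sphericity); correlation rho is varied, with 0.5 as the usual planning value.

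**Power formula (noncentral F):** lambda = f² × N × m / (1 − rho), df1 = (k − 1)(m − 1) = 2, df2 = (N − k)(m − 1).

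**The plan's own figure.** For N = 28, f² × N × m = 0.0625 × 28 × 3 = 5.25 and df2 = 52. At rho = 0.5, lambda = 5.25/0.5 = 10.5 and power is 81.2%. Solving for 90% at N = 28 gives rho = 0.609. The results by correlation are:

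| rho | lambda at N = 28 | power, N = 28 | power, N = 27 | smallest even N for 90% |
|---|---|---|---|---|
| 0.3 | 7.5 | 66.1% | 64.3% | 50 |
| 0.4 | 8.75 | 73.2% | 71.4% | 44 |
| 0.5 | 10.5 | 81.2% | 79.5% | 36 |
| 0.6 | 13.1 | 89.3% | 88.1% | 30 |
| 0.61 | 13.5 | 90.1% | 88.9% | 28 |
| 0.7 | 17.5 | 96.2% | 95.5% | 22 |

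At rho = 0.5 the smallest even N for 80% power is exactly 28. For 90% it is 36, where lambda = 0.0625 × 36 × 3 / 0.5 = 13.5 and power is 90.6%. N = 28 is the 90% answer for rho from about 0.61 to 0.63; at 0.65 the answer is already 26.

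**Other readings at N = 28, rho = 0.5.** None reaches 90%: multivariate version of the test 78.5%; epsilon 0.75 gives 72.2%; between-group main effect 34.5%; f defined without the correlation term 33% to 35%; alpha 0.10 gives 88.9%.

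**Loss allowance (no assumption needed).**
- Correct inflation: 28 / (1 − 0.15) = 32.9, so 33, or 34 with equal arms.
- The figure in the article matches 28 × 1.15 = 32.2.
- Check: 32 × 0.85 = 27.2, so about 27 completers.
- Loss that 32 recruits do cover: (32 − 28)/32 = 12.5%.
- Cost of 27 in place of 28: 81.2% − 79.5% = 1.7 points at rho 0.5; 89.3% − 88.1% = 1.2 points at rho 0.6.

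**What F = 0.25 means on the outcome scale.** Suppose the arms differ by 0, d, d (in SDs of the score at one visit) at the three assessments. The interaction deviations in each arm are then ±(d/3, d/6, d/6), with the first of opposite sign to the other two. Their mean square over the six cells is d²/18, so f = d/√18. Setting f = 0.25 gives d = 0.25 × 4.243 = 1.06 SD. For a gradual pattern (0, d/2, d) it is 1.22 SD.

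**The case against.** The strongest objection is that 81% does not follow from the stated inputs either. It appears only once a correlation of 0.5 and sphericity are supplied, and nothing in the article makes 0.5 more likely than 0.6 for the same pain scale in the same patients over a few weeks. At 0.6 the stated power is reproduced within one point, and above 0.61 it is exceeded. A condensed article may also leave software settings to the full protocol. This stands. It rules out three stronger readings that a reader might infer:

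- **That 28 subjects simply give 81%.** They do so only at correlation 0.5 with sphericity.
- **That an 80% calculation was reported as 90%.** The exact match at 0.5 is suggestive, but 28 is also the 90% answer at about 0.61 to 0.63, so the documents do not prove it.
- **That only differences of about 1 SD could ever be detected.** At 28 subjects and correlation 0.5, a true difference of 0.8 SD in the (0, d, d) pattern still has 56% power. Nor does setting 1.06 SD against the Cohen bands in section 2.5 ("or large (d greater than 0.80) following the method of Cohen") expose an error, because those bands classify observed effects and say nothing about the planning value.

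The loss slip is also small: one patient, or two with equal arms. The article calls 32 a minimum, so recruiting slightly more would be within the plan.

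What the objection does not do is restore the 90%. The article gives a specific power for a specific number, and that claim depends on an input it does not give. The range over ordinary correlations is 66% to 96%, too wide to leave to the reader.

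**Conclusion.** The point holds in conditional form. The 90% cannot be verified from the article. With sphericity it requires a between-visit correlation of about 0.61 or more at 28 evaluable subjects, and between 0.62 and 0.63 at the 27 who would remain. At the usual 0.5 the power is 81.2% with 28 and 79.5% with 27, and 90% would need 36 evaluable. A departure from sphericity lowers these figures further: epsilon 0.75 gives 72.2% at correlation 0.5 and 81.7% at 0.6, both with 28.

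The loss allowance is wrong whatever the correlation, but it costs under 2 points of power. Both points carry over to the AO+MI trial through section 2.4.2. The power figures rest on the group-by-time interaction being the effect powered, as the planned 2 × 3 analysis implies.

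**What to change.** In sections 2.4.1 and 2.4.2, without adding patients:

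1. Retrieve the settings entered in the software and state the correlation between visits, epsilon and the effect tested. This comes first: writing in a figure based on 0.5 would be wrong if a higher value was used.
2. Restate the power at 27 completers: about 80% if the correlation was 0.5, or about 88% to 89% if it was 0.60 to 0.61. Show the range (64% at 0.3 to 96% at 0.7).
3. Correct the loss arithmetic: 32 recruited leave about 27 after 15% loss, or keep 28 if loss is 12.5%.
4. Optionally, add that F = 0.25 corresponds to a between-arm difference in change of about 1.06 SD when the difference appears after treatment and persists at 15 days.

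The cost is the rewording of two paragraphs. The drawback is that the stated power may become less favourable.

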#### 2.4.2. AO+MI-Based Study

The simple size for the AO+MI-based study was calculating taking into consideration the same parameters as tDCS-based study. It being estimated the same sample size of 32 patients.

### 2.5. Data Analyses

The SPSS software package (version 25.00; SPSS inc., Chicago, IL, USA) will be used by a blinded statistician for statistical analysis of the data. Demographic and clinical variables will be presented as mean and standard deviation. A 95% confidence interval (CI) will be taken, considering statistically significant all those values that had a *p* < 0.05. Parametric statistical tests will be used for hypothesis testing (*n* > 30). To show differences in the main variables, an analysis of variance (ANOVA) 2 × 3 of repeated measurements will be carried out taking time and group as factors, being the groups active-tDCS (a-tDCS) vs. sham-tDCS (s-tDCS) in the tDCS-based study and AO+MI-BCI vs. AO-control AO+MI-based study, and the measurements times pre-treatment, post-treatment, and at 15 days post-treatment. If significant differences are found in any of the interactions, a post hoc analysis will be performed with Bonferroni correction. The effect sizes will be calculated by means of the d of Cohen, being classified as small (d between 0.20 and 0.49), medium (d between 0.50 and 0.79), or large (d greater than 0.80) following the method of Cohen.

For the rest of the psychological variables, a Pearson’s correlation with the physical variables will be carried out in order to find relationships between both. Low correlation will be taken as that with values between 0.2 and 0.39; the correlation will be considered moderate when the value goes from 0.40 to 0.79; and high when the value of the correlation is greater than 0.80.

For the analysis of neurophysiological variables rMT, MEP magnitudes will be determined by averaging peak-to peak amplitudes. The ratio of the rMT, MEP amplitude recorded at each post-intervention time-point relative to the baseline rMT will be calculated [(MEP amplitude at each stage–baseline MEP amplitude)/baseline MEP amplitude Å~100]. Statistical analyses will be performed on the calculated test-to baseline MEP ratios. For the CSP values the time will be measured manually in each trial and averaged and the ratio compared to baseline measurement will be also calculated.

A multiple linear regression analysis will be performed to estimate the strength of the associations between the rMT, PPT, CPM, TS, psychological and functional variables, and pain. CPM, TS and neurophysiological variables will be used as predictors. The strength of the association will be examined using regression coefficients (B), *p* values and adjusted R2. Standardized beta coefficients will be reported for each predictor variable.

For the EEG entropy analysis non-parametric Kruskal–Wallis (KW) tests will be performed to compare the distributions, Mann–Withney U test to evaluate the difference between the median values for Pre-intervention/Controls, Post-intervention/Controls or Pre/Post intervention, and non-parametric Wilcoxon rank-sum test for Pre/Post intervention, with a significance level of 0.05 and the alternative hypothesis of unequal values. Thus, small *p*-values will suggest significant differences between populations.

The first part of the analysis will consist of comparing the differences between ON state versus OFF state in pain intensity, conditioned pain modulation, and temporal summation, and the second part will investigate the effects of the intervention on these same variables comparing the differences between ON state versus OFF state. For this analysis repetitive measures of ANOVA will be performed followed by post-hoc test with Bonferroni correction using the interaction of group factor x state factor and time factor.

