### 2.1. Study Design and Participants

The participants will be recruited in PD outpatient’s clinic of the Beata María Ana Hospital of Madrid, Spain. The subjects included will be assessed by a neurologist expert in movement disorders. All patients will be idiopathic PD patients diagnosed according to the UK Parkinson’s Disease Society Brain Bank criteria who suffer from whatever PD-related pain, determined by The Parkinson’s Disease Pain Classification System (PDPCS) [33] and with a pain intensity of 3 out 10 points in the Visual Analogue Scale (VAS) while in ON state, that is, when levodopa is acting. The rest of specific inclusion criteria and the exclusion ones are listed in Table 1 and Table 2. During the protocol, changes in analgesic medication during in the previous week or PD treatment in the previous month will be forbidden and if necessary, will lead to exclusion of the patient. Informed consent for all included procedures (therapies and outcomes measurement), approved by the ethics committee, will be obtained from all subjects before their inclusion, and both studies will follow the principles outlined in the Declaration of Helsinki.

Sensitive data for all participants will be registered separately, anonymized, and guarded according to current data protection European laws. All data will be registered and double checked in a database designed specifically for the studies.

Recruitment in both protocols will be made so placebo and active groups will be matched by age and the recruitment will be stratified in groups of subjects younger than 60 years and older than 60, always ensuring that there is an equitable number of subjects in the two sections.

It is well known that there are gender differences in pain thresholds in healthy humans [34] and some evidence suggests that greater disease severity, female gender and higher doses of mediation are associated with greater pain intensity in PD [35]. For this reason, inclusion of at least one third of female subjects will be assured. Disease severity and total dopaminergic daily dose will be controlled in the final analysis of results.

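### Section 2.1 promises control for disease severity and dopaminergic dose, but the main-outcome ANOVA in 2.5 contains only time and group, and it uses baseline less efficiently than it could

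*Protocol article*

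**What the plan says.** Section 2.5 gives the model for the main variables in both trials: a 2 x 3 ANOVA in which "repeated measurements will be carried out taking time and group as factors". The levels of time are "the measurements times pre-treatment, post-treatment, and at 15 days post-treatment", so baseline is one of the three outcome levels. Bonferroni post hoc tests follow a significant interaction. On software: "The SPSS software package (version 25.00; SPSS inc., Chicago, IL, USA) will be used by a blinded statistician".

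Section 2.1 adds: "Disease severity and total dopaminergic daily dose will be controlled in the final analysis of results". On age, it says that "placebo and active groups will be matched by age" and that "the recruitment will be stratified in groups of subjects younger than 60 years and older than 60".

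Section 2.4.1 sizes the tDCS trial on "King’s Parkinson’s Disease Pain Scale with an estimated effect size of F = 0.25", with alpha 0.05 and 90% power. This gives 28 patients, raised to 32: "Considering a 15% follow-up loss". Section 2.4.2 uses the same parameters for the AO+MI trial.

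**The concern.** Sections 2.1 and 2.5 do not describe the same analysis. One commits to controlling two prognostic variables; the other names a model that has no place for them. With 32 patients per trial, adjusted and unadjusted tests can disagree. If the choice stays open until arms are known, it can follow the result.

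The chosen form also has an efficiency cost. A 2-df interaction over three times, one of them baseline, spreads the test over patterns of no interest and names no time point. Baseline KPDPS would do more as a covariate. Classical repeated-measures ANOVA further needs all three visits from a patient. Some losses may not be random: adverse effects can interrupt treatment (2.2.1), and medication changes lead to exclusion (2.1).

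**Working it through.** **1. Is the covariate commitment met anywhere?**

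| Stated analysis | Terms | Severity and dose? |
|---|---|---|
| Main outcomes, 2.5 | group, time | no |
| ON/OFF comparison, 2.5 | group, state, time | no |
| Multiple regression, 2.5 | predictors: CPM, TS, neurophysiological variables | no |
| Comparison of the two protocols, 2.6 | difference of two mean KPDPS reductions | no |

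The regression mentions functional variables, and UPDRS is the functional outcome. But UPDRS is not among the named predictors, dose is absent, and no arm comparison is described.

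**2. The plan's own sample size.** For the within-between interaction, λ = N·m·f²/(1−ρ), with df (k−1)(m−1) and (N−k)(m−1), k = 2, m = 3, sphericity assumed. The correlation ρ is not stated. With N = 28, f = 0.25 and ρ = 0.5, λ = 28 × 3 × 0.0625/0.5 = 10.5 on 2 and 52 df, and power is 81.2%. The stated 90% is reached at ρ of about 0.61 (90.1%). The point here does not rest on this figure, but it shows which correlations matter.

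**3. Efficiency of baseline adjustment.** Variance factors under compound symmetry:

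- One follow-up: change score 2(1−ρ); baseline-adjusted 1−ρ². At ρ = 0.5: 1.00 and 0.75, ratio 0.75. At ρ = 0.7: 0.60 and 0.51, ratio 0.85.
- Mean of two follow-ups: change score (1+ρ)/2 + 1 − 2ρ; baseline-adjusted (1+ρ)/2 − ρ². At ρ = 0.5: 0.75 and 0.50, ratio 0.67. At ρ = 0.7: 0.45 and 0.36, ratio 0.80.

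**4. Power against the planned test.** A difference D held at both follow-ups gives f² = D²/18, so f = 0.25 corresponds to D = 0.25 × √18 = 1.06 SD. The values 0.85 and 0.70 SD are assumed smaller effects. Simulated power with 14 per arm, compound symmetry, effect at both follow-ups, 20,000 trials per setting (repeat runs agree to about one point):

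| ρ | D (SD) | Interaction, 2 df | Adjusted, one visit | Adjusted, mean of both | One visit + 3 uninformative covariates | Mean of both + 3 uninformative covariates |
|---|---|---|---|---|---|---|
| 0.5 | 0.85 | 61% | 68% | 85% | 63% | 80% |
| 0.5 | 1.06 | 82% | 86% | 96% | 81% | 94% |
| 0.7 | 0.70 | 67% | 69% | 83% | 63% | 77% |
| 0.7 | 1.06 | 96% | 96% | 99% | 93% | 98% |

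At ρ = 0.7 the single-visit contrast gains almost nothing, because it sets aside the 15-day value that the interaction uses. If the effect is present only at the first follow-up (ρ = 0.5, 1.06 SD), the mean of both visits falls to about 46%, against about 86% for the single visit and 81% for the interaction.

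**5. Incomplete patients.** 32 × 0.85 = 27.2, so about 27 complete cases and 5 losses. Interaction power at f = 0.25 and ρ = 0.5 is 79.5% with 27 and 86.6% with 32. The gap of 86.6 − 79.5 = 7.1 points is a ceiling on what could be regained: a patient with one follow-up gives partial information, and a patient with none gives nothing.

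**The case against.** **The planned test is valid, and it does deal with baseline.** The group-by-time interaction compares changes, so a chance baseline difference is subtracted. A reader might infer that such differences are ignored or bias the test; they do not. This stands, and only efficiency is at issue.

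**Age.** A reader might infer that 2.1 also promises age adjustment, or that leaving out the age strata weakens the planned test. Neither follows. Section 2.1 promises matching and stratified recruitment; only severity and dose are promised as controls in the analysis. An age effect that is constant over visits cancels in a within-patient interaction: simulated power was about 0.82 at stratum gaps of 0, 1 and 3 SD. Age group belongs in the revised model because recruitment is stratified on it, not because the plan breaks its word.

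**Missing visits.** The article nowhere says that incomplete patients are dropped. That is inferred from the named method and software, and a missing-data rule may sit in a document not shown. Section 2.4.1 already inflates the sample for 15% loss. This stands, so the matter is a consequence of the method to be settled, not an error of text.

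**Condensed article.** Section 2.1 gives a general sentence and no model, so calling these two rival primary analyses would overstate it. But both statements are explicit, and an unseen plan cannot be assumed to join them when 2.5 itself lists the factors.

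**Conclusion.** The mismatch between 2.1 and 2.5 is established from the text and needs no assumptions: severity and dose are to be controlled, and no stated model controls them. It should be corrected, although the planned interaction test remains valid under randomisation.

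The efficiency gain is conditional. It rests on an unstated correlation, compound symmetry, 14 per arm and an effect at both follow-ups. At 0.85 SD and correlation 0.5, baseline adjustment alone raises power from about 61% to 68% for one visit or 85% for the mean of both; at correlation 0.7 the single-visit gain is about nil. The larger figure may be claimed only if the mean of both visits is the primary contrast and the effect lasts to 15 days. Three covariates that explain nothing cost about 5 points at 0.85 SD, which removes most or all of the single-visit gain.

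**What to change.** Reword 2.1 and 2.5 so that they specify one model, and do so before unblinding:

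- **Outcome:** KPDPS at post-treatment and at 15 days, in a likelihood-based repeated-measures model.
- **Terms:** baseline KPDPS, arm, visit, arm-by-visit, disease severity (baseline UPDRS, if that is the measure meant), baseline total dopaminergic daily dose and age group, stating which group includes age 60.
- **Patients:** every randomised patient with at least one follow-up value. State that patients with none are not recovered, and report them by arm.
- **Primary contrast:** name one arm comparison in advance. The post-treatment visit is safer if the effect may fade; the mean of both visits is stronger if it persists.

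Cost: rewording two sections. KPDPS and UPDRS are already assessed at baseline, age is needed for the strata, dose must be recorded to honour 2.1, and SPSS fits the model. The price is a few degrees of freedom and, if the covariates prove uninformative, several points of power. If the sponsor prefers the unadjusted analysis for that reason, the sentence in 2.1 should be withdrawn instead, openly and before unblinding.

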The mental representation techniques included in the protocol will be Action Observation (AO) and Motor Imagery (MI). In the same way, the combination of AO and MI has shown to synergically increase cortical excitability [27], influencing the activation of cortical areas such as M1 and DLPFC [28]. Specifically in PD, they also have demonstrated to produce corticomotor facilitation [29]. In addition, mental representation training can produce neurophysiological activity similar to actual exercise training [30], which have shown to decrease the intensity and severity of pain in PD patients [31].

There are no studies correlating effects of pain non-invasive neuromodulation with complete neuropsychological evaluation including computerized reaction time tasks and extensive neurophysiological measures such as direct cortical excitability evaluation using TMS and connectivity based in EEG entropy analysis. All these features have been described to be altered in PD and Pain.

The main aim of this study is to conduct two independent parallel randomized controlled trials based on both neuromodulation techniques targeting changes in 1. validated general and specific PD related pain scales 2. psychophysical measurements of pain modulation mechanisms and 3. wide neuropsychological and neurophysiological evaluation. Our main hypothesis is that both active neuromodulation techniques will be superior to their respective control placebo interventions. If this hypothesis is confirmed a further analysis of superiority will be proposed among both protocols.

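### The group-by-time ANOVA named for KPDPS is a non-directional test tied to no visit or arm contrast; one baseline-adjusted contrast would answer the superiority question with equal or better power

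*Protocol article*

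**What the plan says.** The Introduction sets the question: "Our main hypothesis is that both active neuromodulation techniques will be superior to their respective control placebo interventions". Section 2.4.1 fixes the outcome: "The primary outcome was chosen to be King’s Parkinson’s Disease Pain Scale with an estimated effect size of F = 0.25". The calculation was made "taking into consideration the design of two intervention groups and three assessment times", and section 2.4.2 carries the same parameters over to the AO+MI trial.

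Section 2.5 names the test: an "analysis of variance (ANOVA) 2 × 3 of repeated measurements will be carried out taking time and group as factors", with measurements before treatment, after treatment and 15 days later. Its general significance threshold is p < 0.05. The follow-up rule is: "If significant differences are found in any of the interactions, a post hoc analysis will be performed with Bonferroni correction". The contrasts to be corrected are not listed, and no visit is named as deciding.

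Section 2.6 does give an explicit rule, but for a different question. It compares the two therapies with each other on mean KPDPS reduction, two-sided 5%, with a confidence interval that excludes zero. It names no visit either.

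**The concern.** A 2 x 3 ANOVA yields three tests: group, time and group-by-time. None of them is the statement that active beats control after treatment.

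- The group effect averages the pre-treatment score, where no treatment effect can exist, with the two follow-ups.
- The interaction asks only whether the arm difference varies over three visits. It rejects equally for benefit, harm, a rebound between post-treatment and day 15, or a chance baseline imbalance that later disappears.
- The post hoc pairs may compare arms at a visit or visits within an arm, and only the former bear on superiority.

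The same data could therefore be read as superior or not superior according to the line of output chosen. A significant interaction with no surviving arm contrast has no stated conclusion. Sending the question through an omnibus test and then a Bonferroni step can also cost power in a trial of 32 patients.

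**Working it through.** **Inputs from the article.** KPDPS primary, f = 0.25, alpha 0.05, power 90%, 28 evaluable, 32 recruited, 16 per arm, m = 3 visits (2.4.1, 2.5). **Assumed, not in the article:** equal SDs, equal correlation rho of 0.3, 0.5 or 0.7 between visits, and a true arm difference of 0 at baseline and 0.8 SD at both follow-ups.

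**Step 1. Which term does the stated sample size fit?** The plan says: "An α level of 0.05 and a power of 90% was assumed, with a total sample of 28 subjects estimated".

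- Interaction: lambda = f² x N x m / (1 - rho), df 2 and 2(N - 2). With N = 28 and rho = 0.5, lambda = 0.0625 x 28 x 3 / 0.5 = 10.5, and power is 81%. Power reaches 90% with N = 28 at rho of about 0.62. At rho = 0.5, 90% power needs N = 36.
- Group effect: lambda = f² x N x m / (1 + 2 rho), df 1 and N - 2. With N = 28 and rho = 0.5, lambda = 5.25 / 2 = 2.62, and power is 34.5%. For 90% power, N = 116.

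So 28 fits only an interaction (or within-subject) term. Together with the rule that post hoc tests follow an interaction, this indicates that group-by-time was intended.

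**Step 2. Type I error, by what is allowed to support the claim** (simulation, no treatment effect, 16 per arm).

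| What counts as superiority | Chance of a false claim |
|---|---|
| Interaction alone | about 5% |
| Interaction, then a raw arm difference at either follow-up at 0.05/2 | 0.6-1.4% |
| Interaction, then an arm difference in change at 0.05/2 | 3.0-3.8% |
| Group effect or interaction | about 10% (if independent: 1 - 0.95² = 9.75%) |
| Either of those, or an unadjusted arm difference at either follow-up | about 14% |

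**Step 3. Power under the assumed sustained 0.8 SD effect.** For differences (0, d, d) the interaction effect size is f = d / √18, so 0.8 SD gives f = 0.19. The planned f = 0.25 would correspond to d = 1.06 SD.

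- Interaction, N = 32: lambda = (0.64 / 18) x 32 x 3 / (1 - rho) = 3.41 / (1 - rho), that is 4.88, 6.83 and 11.38.
- Baseline-adjusted contrast at post-treatment: residual variance 1 - rho². At rho = 0.5 the noncentrality is 0.8 / √(2/16 x 0.75) = 2.61.
- Baseline-adjusted mean of both follow-ups: residual variance (1 + rho)/2 - rho². At rho = 0.5 the noncentrality is 0.8 / √(2/16 x 0.5) = 3.20.

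The closed forms agree with the simulated powers below to within about one percentage point.

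| Route | rho 0.3 | rho 0.5 | rho 0.7 |
|---|---|---|---|
| Interaction, p < 0.05 | 47% | 62% | 85% |
| Interaction, then raw arm difference at 0.05/2 | 39% | 45% | 54% |
| Interaction, then change-score arm difference at 0.05/2 | 45% | 60% | 83% |
| Baseline-adjusted contrast, post-treatment | 62% | 70% | 85% |
| Baseline-adjusted contrast, mean of both follow-ups | 82% | 86% | 95% |

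A single named but unadjusted post-treatment t test has about 60% power at rho = 0.5. The step from 60% to 70% is therefore due to baseline adjustment, not to naming a contrast.

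**Step 4. Can the choice of visit reverse the answer?** With an effect of 0.8 SD at 15 days only and rho = 0.5, the interaction is significant in 62% of trials and the post-treatment contrast in 5%.

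**The case against.** **This is detail for a full protocol or SAP.** A group-by-time ANOVA with Bonferroni follow-up is conventional, and a condensed article need not list every contrast. That disposes of any complaint resting on silence alone. But 2.5 does choose a test for the primary outcome, and the objection here is to that choice: an omnibus interaction with baseline as a time level, set against a directional claim.

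**The deciding term is signalled.** Step 1 supports this, and it should be accepted that group-by-time was probably meant. The visit and the arm contrast still remain open.

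**The error rate.** A reader might infer that false superiority claims run at two to three times the nominal 5%. The article does not support that. The 10% figure needs the group effect to count as well. The 14% figure also needs unadjusted visit differences to count, which goes against the Bonferroni rule. The p < 0.05 sentence reads as a general reporting threshold.

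**The power comparison.** It is fair to say that part of the gain comes from baseline adjustment. If the post hoc contrasts are change scores, which suits the Abstract's description of outcomes as score changes, the Bonferroni step costs only about 2 to 3 points beyond the interaction. At rho = 0.7 the post-treatment contrast is then hardly better (85% against 83%). The advantage is clear at lower correlations, or if the mean of both follow-ups decides.

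**The between-therapy comparison.** A reader might infer that this undefined result gates a confirmatory comparison. Section 2.6 only says that the comparison will be proposed as further analysis, so little weight rests on it.

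**Conclusion.** The point holds as one about the chosen test. The stated analysis of KPDPS is non-directional, includes the pre-treatment score as a time level, and is tied to no visit or arm contrast, while the hypothesis is superiority over control. Strict use of 2.5 does not inflate type I error.

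The cost is interpretability and power. Over rho 0.3 to 0.7 with a sustained 0.8 SD effect, one baseline-adjusted post-treatment contrast gains 23 to 31 points over the strict route with raw contrasts and 2 to 17 points over it with change contrasts. The mean of both follow-ups gains 12 to 37 points over the change-score route. These sizes depend on the assumed effect, correlations, equal SDs, a Bonferroni divisor of 2 and 16 complete patients per arm. The article gives none of the first four, and its own planning figure is 28 evaluable in total. The change is worth making before unblinding, and it applies equally to both trials.

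**What to change.** In 2.5, state that each trial is decided by one contrast: the active-minus-control difference in ON-state KPDPS, adjusted for the pre-treatment score (ANCOVA), two-sided 0.05, at one named time. That time can be post-treatment or the mean of the two follow-ups; the mean has more power if the effect is sustained. Test the remaining visit (or, if the mean decides, the individual visits in a stated order) in fixed sequence, only after the deciding contrast is significant. Declare the group, time and interaction terms and all within-arm pairs descriptive, so that none of them can support a superiority claim.

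In 2.4, restate the power of that contrast at the existing sample size, with the assumed correlation given.

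The cost is a few lines of text and one power calculation, with no extra patients or data. The downside is that, with post-treatment as the deciding visit, a benefit appearing only at 15 days could not be claimed as confirmatory.
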